# Traditional Chinese acupuncture versus minimal acupuncture for mild-to-moderate knee osteoarthritis: a protocol for a randomised, controlled pilot trial

**DOI:** 10.1136/bmjopen-2016-013830

**Published:** 2016-12-12

**Keywords:** Knee Osteoarthritis, Acupuncture, PAIN MANAGEMENT

## Abstract

**Introduction:**

Knee osteoarthritis (KOA) is one of the most common musculoskeletal disorders. Acupuncture is a popular form of complementary medicine for musculoskeletal conditions, although the evidence is inconclusive. Our objective is to evaluate the efficacy of traditional Chinese acupuncture for pain relief and function improvement in mild-to-moderate knee osteoarthritis (TCAKOA) participants.

**Methods/analysis:**

42 patients will be recruited who have been diagnosed with mild-to-moderate KOA and randomly allocated in equal proportions to traditional Chinese acupuncture or minimal acupuncture. They will receive acupuncture for 24 sessions over 8 weeks. The primary end point is success rate, which will be calculated according to a change from baseline in Western Ontario and McMaster Universities Osteoarthritis Index pain and function scores at 8 weeks. Secondary end points include pain and function measurement, global change, the quality of life and the use of non-steroidal anti-inflammatory drugs (Celebrex, Pfizer) at 8, 16 and 26 weeks.

**Ethics and dissemination:**

Ethical approval of this study has been granted by the Research Ethical Committee of Beijing Hospital of Traditional Chinese Medicine Affiliated to Capital Medical University (permission number: 2016BL-010-02). Written informed consent will be obtained from all participants. Outcomes of the trial will be disseminated through peer-reviewed publications.

**Trial registration number:**

ISRCTN14016893; Pre-results.

## Background

Knee osteoarthritis (KOA) is one of the most common musculoskeletal disorders,^1^ which features as a protracted course of disease. A systematic review shows that the prevalence of KOA is 27.3% in women and 21.0% in men.^2^ A cross-sectional study with 9512 participants aged 50 years or older shows that the prevalence of radiographic KOA was 43.8% in women and 21.1% in men in South Korea.^3^ KOA is one of the leading causes of pain and global disability.

The objective of treating KOA is the alleviation of pain and improving quality of life. Five guidelines^1^
^4–6^ have evaluated treatment effects on key outcomes of KOA (including pain, function and disability). Pharmacologic agents, comprising non-opioid/opioid oral, non-steroidal anti-inflammatory drugs (NSAIDs) oral, intra-articular steroid, topical analgesics and hyaluronate injections are normally used but may be associated with significant adverse reactions (such as peptic ulcer, hypertension and renal damage).^6–8^ Guidelines emphasise the potential role of non-pharmacologic treatment, such as aerobic exercise, electrical nerve stimulation, acupuncture in the treatment. Effective alternatives to pharmacological are therefore desirable.

Traditional Chinese acupuncture (TCA) is a popular form of complementary medicine. In 2005, Germany, Witt and colleagues showed that 8 weeks of the semistandardised acupuncture treatment had significantly alleviated the patient's pain and dysfunction contrasted to the minimal acupuncture (MA) treatment and no treatment condition.^9^ A meta-analysis showed that acupuncture could be considered to be an effective physical treatment for KOA.^10^ However, in the October 2014 publication of *JAMA*, [name] *et al* conducted a Zelen design clinical trial to investigate acupuncture for patients suffering from chronic knee pain. The investigation declared that acupuncture did not convey more advantages compared to sham or better function in sufferers with mild or harsh chronic knee pain.^11^ However, flaws may exist in the trial design, statistics, interpretation of the results.^12–26^ First of all, participants aged ≥50 years with moderate-to-severe chronic knee pain have been recruited. These inclusion criteria may be more suitable for arthroscopic or joint replacement therapy according to the guidance.^1^
^4^ Second, acupuncture intervention is 8–12 sessions in total. The dosage for acupuncture is far from sufficient.^14^
^16^ Third, the team registered trial as studying laser acupuncture, instead of traditional acupuncture.^27^ Researchers had changed the main aim selectively.^14^
^26^ At present, there is a controversy over whether the acupuncture has benefit for KOA.^1^
^4^ Therefore, our aim is to investigate the intensive TCA for participants with mild-to-moderate KOA.

## Materials and methods

### Study design

The study proposes a two-arm, randomised, clinical pilot trial. We will enrol patients from Beijing Hospital of Traditional Chinese Medicine Affiliated to Capital Medical University, Beijing Friendship Hospital and Beijing Jishuitan Hospital. The trial has been registered with ISRCTN at Current Controlled Trials (ISRCTN14016893). Some recruitment strategies include radio and print advertisements through the local web sites and community centre as well as recruiters with general practitioners. The intervention includes 24 sessions of acupuncture and 3 times follow-up (figure 1 and table 1).

**Table 1 BMJOPEN2016013830TB1:** Time to visit and data collection

	Baseline	Treatment phase		Follow-up phase	
	−1 day	0 day	8 weeks	16 weeks	26 weeks
Patients					
Informed consent	×				
Sign informed consent		×			
Medical history	×				
Physical examination	×				
Randomisation		×			
Intervention TCA group (n=21)		24 sessions of TCA			
Comparisons MA group (n=21)		24 sessions of MA			
Outcomes					
WOMAC		×	×	×	×
KOOS		×	×	×	×
VAS		×	×	×	×
SF-12		×	×	×	×
The use of NSAIDs			×	×	×
Participant safety					
Adverse events		×	×	×	×

KOOS, Knee injury and Osteoarthritis Outcome Score; NSAIDs, non-steroidal anti-inflammatory drugs; MA, minimal acupuncture; SF-12, 12-item Short Form Health Survey; TCA, traditional Chinese acupuncture; WOMAC, Western Ontario and McMaster Universities Osteoarthritis Index.

**Figure 1 BMJOPEN2016013830F1:**
[figure not shown]
Trial flow chart. KOA, knee osteoarthritis.

### Inclusion criteria

Age 45–75 years (either sex)Chronic knee pain for the last 6 monthsMorning stiffness ≤30 min.The above-mentioned criteria are consistent with the National Institute for Health and Clinical Excellence (NICE) Guidelines 2014 Edition.^4^
Radiologic confirmation of KOA (Kellgren–Lawrence grade II or III 28).

### Exclusion criteria

Recent acupunctureOther sickness impact the kneeOn surgical operation listNeurologic as well as psychiatric diseasesSevere coagulopathyBreastfeeding or pregnancyNot fitting to take the NSAID (Celebrex, Pfizer) provided.For bilaterally eligible knees, the most symptomatic side will be evaluated in the course of the study.

### Randomisation and allocation concealment

Eligible patients will be randomly assigned to the TCA group or the MA group in a ratio of 1:1 through central automated allocation procedures. An independent statistician generates randomisation sequence by using the SAS V.9.1.3 statistical package (SAS Institute, Cary, North Carolina, USA). Acupuncturists will not involve in the process of randomisation.

The research assistants who collect data, the statisticians who assess outcomes and make statistical analysis will be blinded to group assignment. Participants will not be disclosed information regarding the allocation. Administrators will not be blinded because of the nature of intervention.

### Interventions

The acupuncture protocol follows the CONSORT^29^ and STRICTA.^30^ All acupuncturists have Chinese medicine practitioner licenses, and they have been qualified for at least 10 years. All acupuncturists will receive training in the application of MA. Celebrex will give to participants if their pain intensity ≥80 on a 10 cm visual analogue scale (VAS).^31^

The protocol specifies the intervention of acupuncture to be a 20 min treatment which is applied 3 times weekly for 8 weeks, with 24 sessions in total permitted. Disposable, sterile steel, 0.30×25 mm or 0.30×40 mm needles (Huatuo disposable acupuncture needle, Suzhou Medical Co., Jiangsu, China) will be used in two groups.

### TCA group

Acupuncture points are selected on traditional Chinese Medicine theory of the ‘Bi’ syndrome. These points are composed of 10 local points (*ST34, ST35, ST 36, EX-LE2, EX-LE5, GB33, GB34, SP9, SP10, LV8*) and 11 distal points (*GB31, GB36, GB39, GB41, ST40, ST41, LR3, BL60, SP6, KI3, LI4*) (figure 2). Physicians can choose five to six local points and three to four distal points. Needles will be making an optimum insertion into the skin. Acupuncturists are instructed to achieve ‘De Qi’, and needles will be stimulated manually at least 10 s.

**Figure 2 BMJOPEN2016013830F2:**
[figure not shown]
The points used in the TCA group. TCA, traditional Chinese acupuncture.

### MA group

Non-acupoints in a superficial puncture (2 mm in depth) will be performed in the MA group. Treatment is standardised needling without manual stimulation at seven points at certain distances from TCA group points (table 2). The MA procedure will be given on the same schedule as the TCA group.

**Table 2 BMJOPEN2016013830TB2:** Sham acupuncture points in the MA group

Sham acupuncture points	Location
MP1	Ulnar margin of forearm, midpoint of the connecting line between the rasceta head and condylus medialis humeri
MP2	2 cun above the malleolus lateralis, between the gall bladder meridian and stomach meridian on the distal part of the fibula
MP3	2 cun above the malleolus medialis, in the centre of the tibia surface area (intracutaneous without periost contact, in the direction towards the knee)
MP4	Midpoint of the connecting line between ST36 and GB34
MP5	6 cun above the upper edge of the patella (between the spleen and stomach meridian)
MP6	5 cun above the upper edge of the patella (between the spleen and stomach meridian)
MP7	4 cun above the upper edge of the patella (between the spleen and stomach meridian)
MP8	1 cun under the tibia head, in the medial edge of leg
MP9	Midpoint of the connecting line between GB40 and ST41
MP10	3 cun above the medial edge of calcaneal

One ‘cun’ is defined according to the rules of traditional Chinese medicine as the width of the interphalangeal joint of patient's thumb.

MA, minimal acupuncture.

## Outcomes

### Primary outcome measurement

Success rate will be calculated according to a change from baseline in Western Ontario and McMaster Universities Osteoarthritis Index (WOMAC)^32^
^33^ pain and function scores at 8 weeks. WOMAC function subscale (17 items, scored from 0 to 68) and pain subscale (5 items, scored from 0 to 20) with higher scores represent worse pain and function.

### Secondary outcome measurement

Knee pain will be assessed by WOMAC pain subscale and Visual Analogue Scale (VAS, 0–100, higher scores representing worse pain). WOMAC function subscale will be used to measure physical function. Knee injury and Osteoarthritis Outcome Score (KOOS 0–100, higher scores indicating better function) subscales comprise pain, symptoms, activities of daily living and quality of life.^34^ Health-related quality of life will use the 12-item Short Form Health Survey (SF-12 0–100, higher scores representing better quality of life).^35^ The use of the NSAIDs (Celebrex, Pfizer) will be at 8, 16 and 26 weeks.

Adverse events will be monitored and reported by acupuncturists via open-ended questioning. Patients will be suggested to state any adverse circumstances they go through, comprising discomfort or bruise in the locations pierced by needle, nausea or the feeling of faint after the acupuncture treatment. Every crucial sign and adverse events are going to be investigated and recorded during every visit.

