## Discussion

KOA is a common public health problem and a leading cause of disability. The results of this pilot study are going to concentrate on patients suffering from mild-to-moderate KOA and will investigate whether acupuncture can be a practicable and efficient therapy.

A suitable control group is critical for a well-designed clinical trial. On the basis of the literature review as well as clinical experiences, the acupoints in the MA group do not therapeutically affect KOA. Additionally, the dosage for acupuncture is sufficient. The protocol specifies the intervention of acupuncture to be a 20 min treatment which is applied 3 times weekly for 8 weeks, with 24 sessions in total permitted. Moreover, according to generality for the trial, the wide inclusion criteria will render it more possible that the participants fairly stand for those who have mild-to-moderate KOA. One potential limitation of this study is that acupuncturists are not blinded because of the nature of intervention. However, acupuncturists will not relate to the outcome assessments or data analyses.

The pilot trial will supply the clinical foundation as well as data that are demanded for evaluating the practicability for a large-scale RCT trial in the future.

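### Unblinded acupuncturists collect the adverse events, so the Discussion's assurance that they take no part in outcome assessment does not hold for the safety data

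*Protocol article*

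**What the plan says.** All references are to the protocol article.

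- **Secondary outcome measurement**, within Outcomes: "Adverse events will be monitored and reported by acupuncturists via open-ended questioning". The text then gives examples (discomfort or bruising where needles were placed, nausea, faintness) and says events are recorded at every visit, without saying by whom.
- **Discussion**: "One potential limitation of this study is that acupuncturists are not blinded because of the nature of intervention". The next sentence answers this limitation by saying that "acupuncturists will not relate to the outcome assessments or data analyses".
- **Randomisation and allocation concealment**: "The research assistants who collect data, the statisticians who assess outcomes and make statistical analysis will be blinded to group assignment". Those who administer the intervention are said to be unblinded.
- **Study design, Table 1**: adverse events have their own block, "Participant safety", after the Outcomes block, and are scheduled at day 0 and weeks 8, 16 and 26.
- **Abstract, Methods/analysis**: "Secondary end points include pain and function measurement, global change, the quality of life and the use of non-steroidal anti-inflammatory drugs". Adverse events are not named.

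**The concern.** The article admits one weakness in blinding and answers it with one safeguard. A reader will take that safeguard to cover everything reported under Outcomes, yet the same article gives the safety questioning to the unblinded staff.

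The route of collection matters in this trial. The person needling cannot avoid knowing the arm. Traditional acupuncture uses eight to ten points with manual stimulation to obtain De Qi, whereas minimal acupuncture uses superficial 2 mm needling without stimulation. The events named are mostly minor and self-reported, so the count depends on how the question is put and followed up. An acupuncturist may expect more reactions in one arm and probe accordingly, and patients may play down complaints to the person who treated them.

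At stake is whether the two arms' adverse-event counts can be compared, and whether the same procedure passes unexamined into the larger trial that this pilot is meant to prepare.

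**Working it through.** The article gives no figure to reproduce. The sample size of 42 was set by clinical experience, and no adverse-event rate or power is stated. The check is a comparison of the text, followed by an illustration on assumed rates.

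**Step 1. Who collects the events?** Secondary outcome measurement names the acupuncturists and no one else.

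**Step 2. Are they blinded?** No. The Discussion says so directly, and the randomisation section says the same of those who administer the intervention.

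**Step 3. Does the safeguard cover adverse events?** That depends on whether they count as outcomes, and the article is not consistent:

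| Place | Status of adverse events |
|---|---|
| Outcomes text | Under "Secondary outcome measurement" |
| Table 1 | Separate block, "Participant safety" |
| Abstract | Not among the secondary end points |

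If the outcomes text governs, the Discussion's statement is untrue of adverse events. If Table 1 governs, the statement can be read as covering efficacy only, but then it offers the safety data no protection. On either reading, adverse events are ascertained by unblinded staff with no safeguard described.

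**Step 4. Who asks after treatment ends?** Table 1 schedules adverse events at weeks 16 and 26, and treatment stops at week 8. The sentence on recording at every visit is passive, so the article leaves open whether acupuncturists or others ask at follow-up.

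**Step 5. Illustration.** These rates are assumptions and are not in the document. Let the true rate *p* be the same in both arms, with 90% of events detected in one and 60% in the other.

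False difference = *p* × (0.90 − 0.60) = 0.30 × *p*

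| True rate | Recorded, 90% detection | Recorded, 60% detection | False difference | Patients of 21 |
|---|---|---|---|---|
| 10% | 9% | 6% | 3 points | 0.6 |
| 20% | 18% | 12% | 6 points | 1.3 |
| 30% | 27% | 18% | 9 points | 1.9 |

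One patient in an arm of 21 is 1/21 = 4.8 points. For 27% versus 18%, the half-width of the 95% interval is 1.96 × √(0.27 × 0.73/21 + 0.18 × 0.82/21) = 1.96 × 0.128 ≈ 25 points. A shift of this size would be well inside the sampling noise of the pilot.

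**The case against.** The strongest reply is that this is a mismatch of wording. Table 1 and the abstract keep adverse events apart from outcomes, so the Discussion may have meant efficacy only. Treating practitioners commonly record immediate needling reactions and are best placed to see them. The named events and the visit schedule are the same in both arms, which limits variation in the questioning. No test specific to adverse events is planned beyond a general χ² test for proportions, and the pilot could not resolve a 9-point difference. Moving the question wholly to research assistants would rely on recall at week 8, after 24 sessions, and would lose minor bruising or faintness. Answers about needle sites could also reveal the arm to the people who collect WOMAC.

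Much of this stands. It supports keeping the session records and placing the blinded question after the questionnaires. It does not rescue the Discussion's unqualified statement, because identical prompts do not remove knowledge of the arm.

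Four stronger readings are tempting, and the document does not support them:

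- *That acupuncturists judge the events.* The text has them monitor and report; it gives them no role in grading severity or cause.
- *That blinded assistants are said to collect all data, so the randomisation section is flatly contradicted.* The sentence says that the assistants who collect data are blinded. It does not say that they collect everything.
- *That the safety comparison is biased.* The document shows exposure to bias and gives neither size nor direction.
- *That the efficacy results are compromised.* Nothing shows acupuncturists collecting WOMAC, KOOS, VAS or SF-12.

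**Conclusion.** The point holds for the safety data only. Adverse events are elicited and reported by staff who know the allocation, and the one safeguard the article offers is either untrue of these data or does not reach them. This rests on the text alone and needs no numerical assumption.

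The consequence is an adverse-event comparison exposed to ascertainment bias of unknown size and direction. The 3 to 9 points shown depend entirely on the assumed true rates and detection proportions; they indicate scale and are not an estimate. The primary end point and the other efficacy outcomes are not called into question. The correction is worth making because it is cheap and because the pilot's procedures and data are intended to inform a larger trial.

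**What to change.** 1. Keep the acupuncturists' session-by-session records, which are the right source for immediate reactions.
2. Add one adverse-event question, identically worded in both arms, asked by the blinded research assistants at the existing week 8, 16 and 26 visits. Ask it after the efficacy questionnaires, so that an answer hinting at the arm cannot influence the scores taken at that visit.
3. Report the two sources separately and show the between-arm comparison for each.
4. In the Discussion, limit the statement about acupuncturists to efficacy outcomes, and name unblinded session-level safety ascertainment as a limitation.
5. Give adverse events one status across the outcomes text, Table 1 and the abstract.

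The cost is one extra question per visit, put by staff already present, and a few edits to the text. The blinded source will have longer recall for minor events, which the session records cover. An answer given at week 8 could still be remembered by the same assistant at weeks 16 and 26; neutral wording that does not ask where or how needles were placed reduces that risk.

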### Sample size

The purpose is to accumulate clinical data, obtain the outcome data of the intervention method and prove the feasibility of the study protocol. Forty-two patients will be selected as the sample size according to clinical experience.

### Statistical analysis

The results will be analysed by using the SPSS software (SPSS V.12.0 KO for Windows). The accepted level of significance will be p<0.05. Measurement data were expressed by mean number±SD, enumeration data expressed as a percentage.

The statistical analysis will be carried out based on the theory of intention-to-treat (ITT) analysis as well as per-protocol (PP) analysis. In the case of ITT analysis, missing data will be replaced according to the principle of the last observation carried forward and the maximum likelihood regression analysis. PP analysis will be conducted with patients who have received treatments >16 times and complete the case report form (CSF). χ^2^ Test is going to be performed for the situation of proportions; meanwhile, the analysis of independent sample t-tests is going to be conducted to examine the baseline discrepancies between the two groups. The significance of the differences in the various data in each group will be analysed with a paired t-test. On the basis of the baseline and temporary analgesic medicine dosage adjustment, continuous measurement results will be analysed using covariance test, and logistic regression analysis will be used for the two classification outcomes. Above two analyses will be present as difference in means or advantage ratio with 95% CIs.

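### Missing ITT data are to be replaced by both LOCF and maximum likelihood with neither named as primary, and under this visit schedule LOCF will generally bias the estimates when data are missing

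*Protocol article*

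**What the plan says.** The Statistical analysis section plans analyses "based on the theory of intention-to-treat (ITT) analysis as well as per-protocol (PP) analysis". For the ITT analysis, "missing data will be replaced according to the principle of the last observation carried forward and the maximum likelihood regression analysis". Neither method is tied to an outcome or a visit, and neither is called primary or sensitivity. The same section analyses continuous outcomes by analysis of covariance and binary outcomes by logistic regression, at a significance level of 0.05.

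The primary endpoint is a success rate built from change from baseline in WOMAC "pain and function scores at 8 weeks". The abstract gives the treatment period: "They will receive acupuncture for 24 sessions over 8 weeks". Week 8 is therefore both the primary time point and the end of treatment.

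Table 1 ("Time to visit and data collection") lists WOMAC, KOOS, VAS and SF-12 at day 0 and weeks 8, 16 and 26, with nothing in between. NSAID use is recorded at weeks 8, 16 and 26 only, with no day-0 entry. The table shows 21 patients per arm.

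**The concern.** There are two problems, and both lie in what the text states.

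First, the two methods are not interchangeable. LOCF inserts the last recorded score and assumes that nothing changed afterwards. A likelihood analysis uses the observed trajectories to model the incomplete data. For the same missing score they will usually lead to different results. With no primary method named, the ITT result is not uniquely defined, and the choice could be made after the data are seen.

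Second, this schedule leaves LOCF little to carry. Before week 8 the only earlier score is baseline, so a patient without a week-8 score is recorded as unchanged. After week 8, the score carried may be the one taken as acupuncture ended, which presumes that any benefit persists. The filled-in values then enter the models as if observed, so LOCF standard errors take no account of the imputation.

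At stake are the estimates the pilot will pass on. It tests efficacy at p<0.05 and, according to the Discussion, is meant to supply data for a larger trial. With 21 per arm, each missing patient counted as a failure moves an arm's success rate by up to 1/21, about 4.8 percentage points.

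**Working it through.** The article gives no dropout rate, success rate, effect size or SD, and the sample size has no calculation behind it ("Forty-two patients will be selected as the sample size according to clinical experience"). There is no figure to reproduce. From the article come the visit schedule, 21 per arm and the 0.05 level. **All rates, means and SDs below are assumptions for illustration.** Unless stated otherwise, patients who drop out are assumed to have done as well as those who stay.

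**1. What LOCF inserts**

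| Patient | Score used |
|---|---|
| Missing at week 8 | Day-0 score, so change = 0 |
| Lost before week 8 and not seen again | Day-0 score at weeks 8, 16 and 26 |
| Seen at week 8, then lost | Week-8 score at weeks 16 and 26 |
| Seen at week 16, missing at week 26 | Week-16 score at week 26 |
| NSAID use missing at week 8 | Nothing to carry |

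**2. Primary endpoint, week-8 success.** Zero change is a failure under any success rule that requires improvement. With true success rate p and missing fraction d, the LOCF rate is p(1−d), and the LOCF difference is p1(1−d1) − p2(1−d2).

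- True 0.60 (TCA) versus 0.30 (MA), difference 0.30, equal loss of 10%, 20% and 30%: 0.30 × 0.9, 0.8 and 0.7 = 0.27, 0.24 and 0.21. Power with 21 per arm goes from 0.50 with complete data to 0.43, 0.36 and 0.31.
- Same rates, TCA 30% and MA 10% missing: 0.42 − 0.27 = 0.15. With TCA 10% and MA 30%: 0.54 − 0.21 = 0.33.
- No true effect, 0.50 in both arms, TCA 10% and MA 30% missing: 0.45 − 0.35 = 0.10, odds ratio 1.52. With the loss reversed: −0.10, odds ratio 0.66.
- No true effect and equal loss: 0.

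**3. Continuous outcome at week 8 (WOMAC pain).** With mean improvement m and missing fraction d, the LOCF mean improvement is m(1−d).

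- No true effect, improvement 4 in both arms, 5% versus 25% missing: 4 × 0.95 − 4 × 0.75 = 0.8. With 5% versus 30%: 3.8 − 2.8 = 1.0.
- Simulated false-positive rates (SD of change 3.5, 21 per arm, 5,000 trials, two separate runs): 12.0% and 12.2% for 5% versus 25%; 16.0% and 15.4% for 5% versus 30%.
- Milder imbalance, 10% versus 20%: 6.5–7%. Equal loss of 10%, 20% or 30%: difference about 0 and 4–5% false positives.
- True difference 2.0 with equal loss of 10%, 20% and 30%: 1.8, 1.6 and 1.4.

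**4. Continuous outcome at week 26, patients lost after week 8.** The LOCF mean in each arm is (1−d) × week-26 mean + d × week-8 mean. Assume mean improvements of 6 (TCA) versus 4 (MA) at week 8 and 3 versus 3 at week 26, so a 2-point effect fades to 0.

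| Lost, TCA / MA | TCA | MA | LOCF difference (true 0) |
|---|---|---|---|
| 20% / 20% | 3.6 | 3.2 | 0.4 |
| 30% / 30% | 3.9 | 3.3 | 0.6 |
| 30% / 10% | 3.9 | 3.1 | 0.8 |
| 10% / 30% | 3.3 | 3.3 | 0.0 |

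If the effect fades only to 0.5, equal loss of 10%, 20% and 30% gives 0.65, 0.80 and 0.95, an excess of 0.15 to 0.45.

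**The case against.** - **The bias is conditional.** This stands. It depends on how much is missing, in which arm and why. With no missing data there is none; with no effect and equal dropout the between-arm bias is about zero. A reader might infer that LOCF always biases these results, or that it generally manufactures a treatment effect. The article does not support that: with a real effect and equal loss, the week-8 bias runs toward the null.
- **Nothing predicts a 5% versus 25–30% imbalance.** This also stands. Participants are not told their allocation, and both arms follow the same treatment schedule. Those figures show sensitivity and are not a forecast. Nor is carrying baseline forward misleading for patients who left because they had no benefit.
- **For the primary endpoint, LOCF is missing-as-failure.** Correct, wherever success requires improvement. That is a defensible sensitivity analysis, so the issue for the success rate is which method is primary.
- **Carrying scores forward need not favour lasting benefit.** True in part. Week-16 scores can be carried to week 26, and patients lost before week 8 carry baseline throughout, which works against a lasting benefit. A reader might infer that LOCF must create durability; it does so only if the effect fades, and the last row of the week-26 table shows that it need not even then. The article also does not name durability as the purpose of the follow-up visits.
- **Assigning methods to outcomes is SAP detail, and this is a pilot.** The article does name a likelihood method, and the standard-error criticism does not apply to a likelihood fit. Pilot status limits the consequences. But the text positively commits to LOCF alongside that method, so this is a stated rule and not an omission.

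**Conclusion.** The point holds in conditional form. The article fixes two missing-data methods for the ITT analysis without a primary one, and its own schedule reduces LOCF to zero change at week 8 and to a carried week-8 or week-16 score for patients lost later.

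The direction depends on the pattern of loss: toward the null at week 8 with equal loss and a true effect, either way with unequal loss, and usually toward overstatement at weeks 16 and 26 if the effect wanes. In the assumed scenarios the size reaches 0.8–1.0 WOMAC pain points and about 12–16% false positives at week 8, 0.10 in the success rate with 10% versus 30% missing, and 0.4–0.8 points at week 26. None of the underlying dropout rates, effects or SDs is in the article. This should be corrected, but it does not invalidate the trial.

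**What to change.** Name one likelihood-based method as primary and remove LOCF as a primary method.

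- **WOMAC, VAS, KOOS and SF-12:** a repeated-measures model over weeks 8, 16 and 26 with arm, visit, arm-by-visit and baseline, fitted to the observed data without replacing values.
- **NSAID use:** the same approach without a baseline term, since none is collected.
- **Week-8 success rate:** derive success from multiply imputed week-8 WOMAC scores, with missing-counted-as-failure as a labelled sensitivity analysis.
- **Analgesic adjustment:** the current text also adjusts for analgesic dosage. State explicitly whether that adjustment carries over, so that it is not lost by accident.

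The cost is revised wording and a little more programming, possibly outside the SPSS version named in the article. No new data are needed, and the article reports that recruitment was still under way. The likelihood model and the multiple imputation, as usually applied, rest on a missing-at-random assumption, which should be stated.
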